### Participants and procedure

An a priori power analysis revealed that a sample of N = 182 would be necessary to obtain a power of .8. Three large institutes for residential treatment, including Pluryn De Hoenderloo Groep (youth care), Pluryn Jan Pieter Heije (care for youth with intellectual disability), and Karakter child and adolescent psychiatry (youth mental health care) will participate in this study. All treatment groups with adolescents between 12 and 16 years old, boys and girls, with a full-scale IQ of 50 or higher will be invited to participate. There are 20 treatment groups with 8–10 adolescents each that meet these criteria, of which are 8 youth care groups (Pluryn De Hoenderloo Groep), 8 groups for youth with MID (Pluryn Jan Pieter Heije), 2 mental health care groups, and 2 mental health care groups for youth with MID (Karakter child and youth psychiatry). Five groups (40–50 adolescents) include only boys, three groups (24–30 adolescents) include only girls, and twelve groups (96–120 adolescents) include both boys and girls. If the participants in the groups agree to participate, they will receive more information about the program and training, and the CDI-2 will be administered as a baseline assessment for depression (T1). Subsequently, groups will be randomly allocated to either one of both conditions. From the treatment groups selected, none of the adolescents will be excluded in order to avoid stigmatization and social exclusion. All parents will receive a letter with information regarding the goals and content of the study and will be asked permission for their child’s participation by passive informed consent. Since not all parents may understand written Dutch, given the expected social and ethnic characteristics of the sample, group care workers will ask the parents if they have understood the letter and if they have any questions. Parents and adolescents are free to withdraw themselves from the study at any time. Next, 2–3 permanent staff members of groups allocated to the intervention condition will receive a three-day training conducted by two experienced and licensed psychologists with broad expertise in cognitive behavioural therapy. Subsequently, T2 will be administered, and the training program will start.

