**Fig. 1 Fig1:**
[figure not shown]
Study design

Randomization will be conducted by an independent statistician of the Radboud University Nijmegen and will take place on the level of the naturally existing treatment groups rather than on the level of individuals (clustered randomization). In the Netherlands, residential treatment groups usually comprise 8–10 adolescents that follow the same treatment program, live in the same building, and are usually taken care of by a permanent staff of nurses and social workers. The benefits of randomisation of natural groups are as follows: (1) it minimizes contamination among adolescents and staff; (2) it best reflects the natural situation in residential treatment settings, increasing the ecological validity of the study; (3) adolescents who will receive the intervention program know each other already and are used to undertake therapeutic activities together; and (4) staff members who will conduct the program already have a therapeutic relationship with the adolescents. Stratification on the cognitive level (MID versus non-MID) will be needed in order to ensure that the cognitive level is evenly distributed across the control and intervention conditions.

To test the effectiveness of the intervention, all adolescents and their parents will complete self-report questionnaires approximately one month before the start of the program and before adolescents know to which condition they are assigned (Baseline, T1), approximately one week before the start of the program (T2), immediately after the program (T3), and three months after the end of the program (T4). Adolescents in the control condition will complete the questionnaires at exactly the same time points. To make sure that all adolescents (MID and non-MID) understand the questionnaires, adolescents will be assisted in filling out the questionnaires by a trained research assistant that is blind to condition.

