### Strengths and limitations

An asset of the proposed study is that it is one of the first studies examining a program to increase emotional resilience in a residential setting and is also the only Dutch CBT program specifically adapted to adolescents with MID. There is a strong need for interventions addressing internalizing problems in this complex target group, given that youth in residential settings often display elevated levels of internalizing problems, but problems are often unrecognized and residential treatment is not sufficiently effective in reducing internalizing symptoms. Other than most RCTs, the present study not only examines effectiveness but also takes into account the possible mediators of change. Moreover, the study has a robust design, with a relatively large sample and assessments including multiple informants, and it takes place in a natural setting to optimize ecological validity and generalizability into real-life settings. Another strength is that the program will be group administered, thus enabling all adolescents in treatment groups to participate and minimizing stigmatization. This also optimizes opportunities for adolescents to implement the skills taught in OVK to their daily lives. Finally, the OVK program contains only eight sessions and takes place at treatment groups where adolescents live, therefore a minimal drop-out rate is expected.

A limitation of this study is the open rather than blind design; as participants and other informants included in the assessments (parents and/or caregivers) are aware of the condition they are in, self-reports may be biased. Nevertheless, research assistants administering the questionnaires are blind to condition. Moreover, participants will be told that the program aims to ‘help them to better deal with difficult situations’, without mentioning the specific effects expected on the outcome variables, thereby minimizing expectation effects. Finally, the last planned follow-up assessment is three months. A longer follow-up period would have offered better chances to map longer-term effects of the intervention; however, then a large drop-out rate would be expected, since the follow-up period would extend the relatively short (6–12 months) period during which adolescents are in residential treatment.

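### The article's two accounts of the procedure disagree on when parents are asked for permission, and in one of them refusal could depend on the allocated arm

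*Protocol article*

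**What the plan says.** Two sections of the protocol article bear on when parents are approached.

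**Participants and procedure** is written as a sequence. Adolescents come first: "If the participants in the groups agree to participate, they will receive more information about the program and training", with the CDI-2 taken as the T1 baseline. Then: "Subsequently, groups will be randomly allocated to either one of both conditions". A rule on inclusiveness follows, that "none of the adolescents will be excluded in order to avoid stigmatization and social exclusion". Next comes the parent step: "All parents will receive a letter with information regarding the goals and content of the study and will be asked permission", by passive consent. Because some parents may not read Dutch, group care workers check that they have understood the letter and invite questions. The section then moves to training of staff in the intervention groups, and after that to T2.

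**Design**, in the text after Figure 1, says that "all adolescents and their parents will complete self-report questionnaires approximately one month before the start of the program". This is T1, and it falls before adolescents know their condition. Whether parents or staff know the condition by then is not stated.

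Two further statements matter. Whole treatment groups are randomised, not individuals. Strengths and limitations concedes that "participants and other informants included in the assessments (parents and/or caregivers) are aware of the condition they are in".

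**The concern.** Randomising groups makes the arms comparable for the adolescents whose participation was settled before allocation. If parents can object afterwards, and know or can learn the arm, the set of adolescents analysed may be shaped by the arm itself.

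The decision could differ between arms. Parents of an intervention group would be agreeing to an eight-session programme as well as questionnaires; parents of a control group would be agreeing to questionnaires only. The people who speak with them are care workers on the same groups, and they are not blind in an open trial. An intention-to-treat analysis does not remove the resulting difference if the adolescents whose parents refuse are left out of it.

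**Working it through.** **Step 1. The two accounts side by side**

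| Event | Participants and procedure | Design |
|---|---|---|
| Adolescents agree; T1 CDI-2 | before allocation | about one month before the programme |
| Parents complete questionnaires | not mentioned | at T1 |
| Allocation | after T1 | adolescents do not yet know it at T1 |
| Parent letter and permission | told after allocation, before staff training | not mentioned, but contact by T1 is implied |

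Parents cannot fill in T1 forms if the study first reaches them after T1 and after allocation. Either the letter goes out earlier than the first account suggests, or parents do not take part at T1 as the second account says.

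**Step 2. How firm is the order?** Allocation, staff training and T2 each carry a sequence word (*Subsequently*, *Next*, *Subsequently*). The letter sentence has none; its timing comes only from standing between allocation and training. The order is therefore an inference, though it is the one that a site following the text would draw.

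**Step 3. Illustration of size.** The article states no refusal rate, so there is no figure of its own to reproduce on this point. Its sample size serves as an input and does reproduce: 102 × 1.49 = 151.98, and 151.98 × 1.2 = 182.4, stated as 182 (91 per arm).

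Assumptions, not taken from the article:
- r = difference between arms in the share refusing after allocation, 5% to 20%;
- g = difference in mean CDI-2 between those who refuse and those who stay, 0.25 to 1.0 SD, the same in both arms.

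Shift in the comparison before covariate adjustment = r × g:
- low: 0.05 × 0.25 = 0.0125 SD, which is 2.5% of d = 0.50;
- middle: 0.10 × 0.50 = 0.05 SD, 10%;
- high: 0.20 × 1.0 = 0.20 SD, 40%.

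Effect on the one-sided 5% test, if the shift favours the intervention. After 20% loss each arm has 91 × 0.8 = 72.8. With the 1.49 inflation, the standard error in SD units is √(2 × 1.49 / 72.8) = 0.202.
- Shift 0.05: P(Z > 1.645 − 0.05/0.202) ≈ 0.08.
- Shift 0.10: P(Z > 1.645 − 0.10/0.202) ≈ 0.12.

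A shift in the other direction would hide benefit instead. These figures show sensitivity only; they do not estimate what will happen.

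**The case against.** The case on the other side is substantial.

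- **The timing is not stated.** The letter sentence stands among standing rules, such as the freedom to withdraw at any moment, which is plainly not a step in a sequence. Together with parents' part at T1, the text can be read as placing the letter early. This stands, and it is why the point is an inconsistency and not a proven flaw.
- **Much is settled before allocation.** Adolescents' agreement and the baseline CDI-2 come first, and consent is passive, so a parent who does nothing leaves the child in. This stands and probably limits the effect.
- **Nothing says that the letter reveals the arm.** It covers goals and content, and participants are told only a neutral aim. This stands in part: parents are described as aware of the condition, and the staff who answer their questions would know it.
- **The analysis adjusts.** Baseline differences, including depressive symptoms, are to be checked and entered as covariates, and loss of respondents is to be handled by multiple imputation. Adjustment deals with what T1 measured, not with unmeasured reasons for refusing. Imputation helps only if refusers' T1 data stay in the data set.

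A reader might go further and infer that adolescents admitted after allocation also enter the trial, from the no-exclusion rule together with the "relatively short (6–12 months) period during which adolescents are in residential treatment". The article does not support that. The rule is about stigma, no sentence enrols newcomers, and dismissals are counted as drop-out with no mention of replacement. Length of stay therefore bears on attrition, not on selection into the comparison.

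**Conclusion.** The point holds as an inconsistency with a possible consequence. The two sections cannot both be followed on when parents are first approached. If the Participants and procedure order is used, parental refusal could depend on the arm, and baseline adjustment would correct this only in part.

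It would be too strong to say that the protocol recruits after allocation, or that knowledge of the arm decides who is analysed. The timing is inferred from sentence order, and adolescents' own agreement precedes allocation.

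The size cannot be derived from the article. The range of 0.0125 to 0.20 SD rests wholly on the assumed refusal difference and the assumed CDI-2 difference, and it is before adjustment. The point should nevertheless be settled, because the remedy costs almost nothing and closes the route completely for objections made at the permission stage.

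**What to change.** Reconcile the two sections with one explicit order: the parent letter goes out, parents' questions are answered and the objection period closes, all before T1 and before allocation is made or disclosed to parents and staff. T1 and allocation then follow.

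Add one sentence to the intention-to-treat statement: the analysis includes every adolescent with no objection recorded when that period closes. Report any later refusals and withdrawals by arm, with the T1 CDI-2 of those concerned where its use is still permitted. The right to withdraw at any time is unaffected.

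The cost is that letters and conversations with parents happen a few weeks earlier. No extra visits, staff or measurements are needed, and attendance at sessions can stay as inclusive as planned.

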### The intervention

#### Program theory

The program OVK is based on the principles of cognitive behavioural therapy [25]. Cognitive behavioural therapy (CBT) aims to alter maladaptive thoughts, feelings, and behaviour by teaching people skills to recognize their automatic negative thoughts and the consequences on their feelings and behaviour, to challenge the validity of their thoughts, and to change maladaptive thoughts into more helpful, adaptive thoughts. If adolescents successfully adopt these skills, their maladaptive self-schemas will no longer be reinforced, thus creating the opportunity to change negative self-schemas into more adaptive, positive self-schemas. In this way, negative life events will no longer trigger depressive self-schemas, making adolescents more capable and resilient when resolving developmental challenges they encounter in the transition into adulthood. Adolescence provides an ultimate opportunity to preventively alter self-schema’s of depression, since cognitive functions and structures are not yet fully developed and still malleable [26].

#### Program structure

The original OVK program (for a description, see [27, 28]) was reviewed in an expert group of scientists and clinicians in the field of residential youth and mental health care, resulting in the following structural adaptations:Treatment duration: Given the relatively short treatment periods in residential care, the program was shortened from 16 to 8 sessions of 45 min, including only the CBT component of the original program.Integration in existing treatment plans: The program was incorporated in the existing treatment plans by formulating goals for the training that matched treatment plans. To integrate the taught techniques in the therapeutic living environment, adolescents will make an individual implementation plan together with the group care workers (‘signaleringsplan’).Fit with the target group: To make the program suitable for a target group of youth with complex problems, the current program contains less verbal and more practical and visual elements (e.g. pictograms, video clips), the text and layout of treatment materials were simplified, and efforts were made to optimize generalizability to daily life (e.g. use of a personal implementation plan, inclusion of parents and supervisors in home work exercises, and more attention to personal experiences of youth). For youth with MID, a parallel version of the program was created, following the suggestions of the expert group and Didden [20]: (1) the MID version contains less verbal and more visual and practical exercises than the non-MID version, and language is simplified; (2) in the MID version, adolescents receive more support from social workers (e.g. help in homework, help in detecting inaccurate thoughts and challenging their thoughts) than in the non-MID version in order to adapt to their cognitive ability and to optimize generalizability to daily life; (3) the trained skills are taught through smaller sub-steps; and (4) techniques that require higher-order cognitive reasoning (e.g. reasoning about a hypothetical situation; reasoning about other people’s thoughts) are eliminated and replaced by more concrete and behaviour-oriented techniques (e.g. teaching self-instruction and behavioural alternatives in situations adolescents encountered in real life).

In the final program, adolescents are trained in the following cognitive-behavioural skills:to recognize and describe feelings and thoughtsto detect inaccurate thoughtsto evaluate the accuracy of inaccurate thoughtsto challenge inaccurate thoughts by considering alternative interpretationsto use behavioural techniques to regulate emotions (relaxation exercises, distraction of thoughts).

The sessions included group talks, individual and group exercises, and video fragments. After each session, the adolescents are assigned a homework task that takes approximately 15 min. The program will be delivered by permanent staff members at each location that will receive a 3-day training session covering the theoretical principles of CBT, practical training in CBT skills and therapeutic techniques, and an in-depth covering of the intervention protocol. The training will be delivered by experienced and licensed psychologists with broad expertise in CBT. All staff members will receive a detailed manual of the intervention program, and they are offered the opportunity to contact the research team for additional support during program delivery.

### Measures

#### Descriptive and clinical variables

For all participants, demographics (age, birth country of adolescent and that of parents), information on treatment setting (mental health care, youth care, care for youth with MID), IQ-scores, DSM-IV diagnoses, pharmacological information (medication use and dose) and juridical status (whether and when a child protection measure was imposed) will be retrieved from their treatment charts.

#### Primary outcome measures

The primary outcome will be depressive symptoms as measured by the Dutch version of the Children’s Depression Inventory 2 (CDI-2) [29]. The CDI-2 includes both a self- and parent-report questionnaire containing 28 and 17 items respectively. Each item consists of three sentences describing depressive symptoms graded according to severity, from 0 (symptom not present) to 2 (symptom clearly present). A higher total score means more depressive symptoms. This instrument has good reliability and consistency [30], and although no psychometric data are available for youth with MID, the original CDI shows good reliability in samples of adolescents with MID [31, 32].

#### Mediators

Possible mediators include negative cognitive styles and coping styles.

##### *Negative cognitive styles*

will be measured with the Children’s Negative Cognitive Errors Questionnaire – Revised (CNCEQ-R) [33], which is a revised version of the CNCEQ [34]. The CNCEQ-R consists of 16 items that each describe an ambiguous scenario and a possible negative thought. Adolescents rate whether the described thought corresponds to what they would think on a 5-point scale, from 1 (‘not at all like I would think’) to 5 (‘almost exactly like I would think’). Five subcategories of cognitive errors are defined: personalizing, overgeneralizing, threat conclusion, selective abstraction, and underestimation of the ability to cope. The original version of the CNCEQ has a good internal consistency and test-retest reliability among clinical samples [34]. Little is known about the psychometric qualities of de CNCEQ-R in samples of adolescents with MID.

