The hypotheses will be tested with mixed effects linear regression analyses in Mplus6. Because adolescents are nested within groups and groups are nested within locations, a three-level analysis is most appropriate to account for the non-independence of the data. However, this technique requires relatively large numbers of clusters (~25) and members in clusters (~25) [45]. With 3 locations, 20 clusters, and 8–10 members in each cluster, a multilevel analysis is not suited. To correct for the problem of the potential non-independence of the data for the clusters, the TYPE = COMPLEX procedure in Mplus will be used. This procedure corrects the standard errors of the parameter estimates for dependency. These standard errors are unbiased estimates and will be greater in comparison to the standard errors derived from individual level analysis. The effect of location will be tested by introducing dummy variables in the regression equation. We will check for possible baseline differences between the two conditions in background variables (e.g., age, sex, and ethnic background, cognitive capacities) and depressive symptoms. These variables will be entered as covariates in the regression equation.

To explore the mediating role of adolescents’ cognitive styles, coping styles, and therapeutic climate, mediation analyses will be performed using Mplus. The significance of indirect paths will be tested via bootstrap sampling. Moderating effects of age, gender, and treatment setting on the relation between depression and anxiety will be explored by entering the moderating variables as predictors for depression/anxiety. The moderation and mediation analyses will be done for the OVK and TAU conditions separately. Reporting of the results of the study will be in accordance with the CONSORT statement [46].

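### The cognitive-style mediator (CNCEQ-R) is of unestablished validity for the MID half of the sample, who also receive a different programme version, yet the mediation plan has no MID term or split

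*Protocol article*

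**What the plan says.** Under Negative cognitive styles, the protocol article states: "The CNCEQ-R consists of 16 items that each describe an ambiguous scenario and a possible negative thought". The response task follows: "Adolescents rate whether the described thought corresponds to what they would think on a 5-point scale". On measurement quality it says "The original version of the CNCEQ has a good internal consistency and test-retest reliability among clinical samples", and then: "Little is known about the psychometric qualities of de CNCEQ-R in samples of adolescents with MID".

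Under Program structure, the parallel MID version is described as one in which "techniques that require higher-order cognitive reasoning (e.g. reasoning about a hypothetical situation; reasoning about other people’s thoughts) are eliminated". Concrete, behaviour-oriented techniques such as self-instruction replace them. The same list gives MID adolescents extra help in detecting and challenging inaccurate thoughts.

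Participants and procedure lists, beside eight youth care groups, "8 groups for youth with MID (Pluryn Jan Pieter Heije), 2 mental health care groups, and 2 mental health care groups for youth with MID". Design makes cognitive level (MID or not) the stratification factor and has a trained assistant help every adolescent with the questionnaires.

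Goals and hypotheses makes the identification of mechanisms the second aim, with the expectation that cognitive bias and coping mediate the effect on depression. Statistical analyses says: "To explore the mediating role of adolescents’ cognitive styles, coping styles, and therapeutic climate, mediation analyses will be performed using Mplus". It adds that mediation and moderation will be run within each condition separately. The moderators named there are age, gender and treatment setting, and they are attached to the relation between depression and anxiety.

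**The concern.** The plan gives a cognitive reason for removing a kind of task from the MID programme. It then scores the proposed mechanism in the same adolescents with an instrument that rests on a closely related task. It cites no evidence for the scale in MID. For the primary outcome it at least points to MID data on the predecessor of the CDI-2.

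Two things could differ by MID status: how well the score measures cognitive style, and how far the programme version moves it. Either would make the cognitive-style path differ between the two halves of the sample. The stated analysis does not allow for that, although MID status is the randomisation stratum and determines the programme version.

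At stake is the answer to the second aim. If no mediation by cognitive style is found, the reader could not tell whether the mechanism is absent, whether the scale works poorly in MID, or whether the MID version works by another route. If mediation is found, it could be credited to MID adolescents when the non-MID groups supply it.

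**Working it through.** **Share of the sample.** MID groups: 8 + 2 = 10 of 20, or 50%. With 8–10 adolescents per group that is 80–100 of 160–200 eligible. With equal group sizes it is about 91 of the planned 182.

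**The plan's own sample size.** 102 × 1.49 = 151.98, and × 1.2 = 182.4, which reproduces 182. Nothing here changes that figure. After 20% loss, 182 × 0.8 ≈ 146 remain. Divided by the plan's clustering factor, 146/1.49 ≈ 98.

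**Does the stated analysis already cover MID?**
- Treatment setting is a moderator of a different relation. It is also not the same as MID status, because two of the ten MID groups are in mental health care.
- Cognitive capacity is named among the possible covariates. A covariate adjusts means. It does not allow for unequal reliability or an unequal programme effect on the mediator.
- The split by condition is not a split by MID. Within one condition there is also no path from condition to mediator, so an indirect effect of OVK needs both conditions in one model.

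**Illustration of size.** The plan gives no reliabilities or shifts, so these are assumptions: half the sample MID; OVK shifts the mediator by 0.5 SD in non-MID groups; mediator-to-depression slope 0.4; reliability 0.8 in non-MID; equal observed spread in both strata. Observed paths then scale with the square root of reliability, and the pooled path is roughly the average of the two strata.

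- Non-MID: (0.5 × √0.8) × (0.4 × √0.8) = 0.447 × 0.358 = 0.160.
- MID reliability 0.4, equal shift: condition path (0.447 + 0.316)/2 = 0.382; depression path (0.358 + 0.253)/2 = 0.305; product about 0.117, or 73% of 0.160.
- MID reliability 0.4, half the shift: condition path (0.447 + 0.158)/2 = 0.303; 0.303 × 0.305 = 0.092, or 58%.
- Milder case, MID reliability 0.6, equal shift: 0.417 × 0.334 = 0.139, or 87%.

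Simulation of the same model gave 0.116, 0.091–0.092 and about 0.139. If error is instead added on top of the true score, so that observed spread differs, the pooled value at MID reliability 0.4 with equal shift is 0.4 × 0.5 / (1 + (0.25 + 1.5)/2) = 0.107, or 67%.

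Within a single condition, as the article words it, only the mediator-to-depression path is affected: 0.305/0.358 = 85% at MID reliability 0.4 under equal spread.

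**Would it help to use the non-MID groups alone?** Simulated power of a joint-significance test (individual level, n = 146):

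| MID reliability, shift | Both strata | Non-MID only |
|---|---|---|
| 0.8, 0.5 | 0.76 | about 0.4 |
| 0.4, 0.5 | about 0.6 | about 0.4 |
| 0.4, 0.25 | about 0.4 | about 0.4 |
| 0.4, 0 | about 0.26 | about 0.4 |

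At an effective n of 98, reliability 0.4 gives about 0.38 against 0.23 with equal shift, and about 0.27 against 0.23 with half the shift. The non-MID groups alone are clearly better only if the MID version does not move cognition at all.

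**The case against.** A reader might infer that the MID scores are invalid by design and that a mediation result across both strata cannot be interpreted. The article does not support that.

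- Program structure removes training techniques that adolescents would have to learn and apply. Rating a supplied thought against one's own, with a trained assistant at hand, may be a lighter task. The article says little is known about the scale in MID; it does not say the scale fails.
- The MID version still contains work on thoughts. MID adolescents get help in detecting and challenging them, and the list of skills for the final programme makes no MID exception. A zero shift in MID is therefore an extreme case without support in the text.
- The psychometric gap is disclosed, and the mediators are called possible and their role exploratory. Coping style, the other mediator under the second aim, is not touched by this argument.
- The article runs mediation within each condition, so the model with both conditions used for the figures is not the stated one. Pooling over MID status is inferred from the absence of any MID split.
- Reliability tables by stratum are the kind of detail a condensed article may leave to a fuller plan.

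Most of this stands, and it limits the point to ambiguity and likely attenuation. It does not remove the point. The article does specify how mediation will be split and where moderators enter, and what it specifies leaves out the one factor on which both the programme version and the doubt about the scale turn. Assistance can help an adolescent understand an item, but it does not change the judgement the item asks for.

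**Conclusion.** The point holds in a limited form. For half of the sample the validity of the CNCEQ-R is unestablished, the programme version differs, and the stated mediation analysis has no MID term. An indirect effect across both versions would be pulled towards zero if the scale is less reliable in MID or moves less there: to about 87% of the non-MID value in a mild assumed case, and to 73% and 58% in less favourable ones. A null cognitive-style result would then be hard to read.

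These sizes rest on assumed reliabilities, shifts and slope, and on purely random measurement error. A systematic response tendency shared with the self-reported depression score could act in the other direction. Neither the effect on depression nor the sample size is in question.

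**What to change.** In Statistical analyses:

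1. Fit the cognitive-style mediation with both conditions in one model, replacing the condition-by-condition analysis for this mediator.
2. Let MID, the stratification factor, moderate the path from condition to cognitive style and the path from cognitive style to depression.
3. Report the indirect effect by MID stratum alongside the overall one.
4. Report CNCEQ-R internal consistency by stratum at the first pre-programme assessment where the scale is given. Participants and procedure names only the CDI-2 at T1, whereas Design speaks of questionnaires generally, so this may be T1 or T2.
5. Limit any mediation claim for MID adolescents to what their stratum shows.

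The MID groups should not be dropped, and pooling should not depend on internal consistency alone, since consistent answers are not necessarily valid ones.

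The cost is a few sentences. The scale and the stratum are already part of the plan. The drawback is precision: with about 10 clusters per stratum, the stratum-specific estimates will be imprecise and should be labelled exploratory.
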